### Data collection and management

The necessary clinical data are extracted from the patient’s medical records and source documents, providing essential information on demographics, medical history, diagnosis, treatments, and any adverse event or complications that occurred during hospitalization or FU. A dedicated data collection form is used to systematically record all clinical information and study-required analyses, ensuring consistency, accuracy, and reliability in data gathering. For each enrolled patient, a Case Report Form (CRF) is created. The CRF is a document used in clinical research to collect and manage data in compliance with regulatory requirements and study protocols. It serves as a crucial tool for ensuring data integrity, tracking patient progress, monitoring adherence to the study design, and facilitating statistical analyses. By maintaining a structured approach to data collection, this study aims to enhance the reliability and validity of findings, ultimately contributing to improved patient care and medical advancements.

### Statistical methods

The sample size for the trial was calculated through an *a priori* power analysis using G*Power software (version 3.1.9.6, University of Kiel, Germany), considering a power of 0.80 and a confidence level of 95% (one-tailed Fisher’s exact test). The effect size, in terms of odds ratio, was calculated based on spinal fusion literature data (23, 24). Ricart et al. (26) reported spinal fusion rates of 90% in patients treated with autograft + demineralized bone matrix (DBM), compared to 70% in those treated with allograft and bone marrow aspirate (BMA) (OR = 3.9). Slosar et al. (27) reported SF rates of 93% in patients treated with allograft and bone morphogenetic protein (BMP) compared to 73% of those treated with allograft alone (OR = 5.3). Therefore, the effect size was set at an OR of >4.8, assuming a higher SF percentage in the group treated with vBMA clot combined with allogeneic bone chips (>91%) compared to the group treated with allogeneic bone chips alone (<70%). For each treatment group, the minimum number of patients is *n* = 58, including a 20% drop-out rate.

Statistical analysis is conducted using R software and related packages, such as ggplot2, for graphical data representation. A *p-*value of < 0.05 is considered statistically significant. All data are recorded in an electronic dataset containing continuous variables (e.g., age, growth factor expression, and bacterial time kill results), categorical nominal variables (e.g., gender, diagnosis, and treatment), and categorical ordinal variables (e.g., Brantigan SF classification, VAS score, and ODI score). A univariate analysis should be conducted to determine the distribution, central position (e.g., mean and median), and dispersion (e.g., variance, standard deviation, and interquartile range [IQR]) of quantitative variables. For qualitative variables, frequency distributions are reported. Continuous variables with skewed distributions are transformed and assessed to achieve normality.

To prevent information loss and the introduction of potential selection bias, missing values may be imputed. In cases with very few missing values, a single imputation method is applied; otherwise, a multiple imputation method is applied, providing valid inferences under the missing at random (MAR) assumption. To perform multiple imputations, the Multivariate Imputation by Chained Equations (MICE) R package is used.

After defining and managing the dataset, bivariate or multivariate analyses are carried out to evaluate relationships between variables. In the case of continuous data, the independent Student’s *t*-test and Wilcoxon rank-sum test are used to compare data between the two treatments for parametric and non-parametric data, respectively. Linear models are applied for regression analysis. In the case of categorical dichotomous data, Fisher’s Exact test or chi-squared test is used to compare proportions between the two treatments, and logistic models are applied for regression analysis. For non-dichotomous categorical data, the Mann–Whitney U-test or the Wilcoxon rank-sum test is used to compare ordered outcomes between the two treatments, and the Ordinal Least Squares, Cumulative Link, or Multinomial Logistic models are applied for regression analysis.

Since the variable of the primary outcome is dichotomous (fusion or no fusion), it is analyzed in relation to age (categorized) and gender through logistic regression models. Additional factors (e.g., follow-up time points) and covariates (e.g., platelet-derived growth factors) influencing spinal fusion may be included in the model. To combine covariates into a multiple logistic regression model, collinearity and predictive power are assessed. The results are reported as odds ratios (ORs) with corresponding 95% confidence intervals (CIs). The primary outcome is also assessed through appropriate stratifications of the population based on the presence or absence of specific comorbidities.

Given the longitudinal nature of FU data (e.g., VAS, ODI, and spinal fusion grading across multiple time points), repeated-measures ANOVA or linear mixed-effects models are applied to assess both within-subject (time) and between-group (treatment) effects, accounting for intra-subject correlation and missing data. This finding allows for a robust evaluation of changes over time and treatment efficacy.

Finally, after defining the most reliable models based on multiple criteria (e.g., Akaike Information Criterion, R^2^), diagnostic tools are used to evaluate model assumptions and identify potential influential observations. The same analysis process is implemented for the other regression models related to secondary outcomes, with appropriate diagnostics applied.

Data collection and statistical analysis are standardized and blinded.

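### The 80% power holds only for a one-tailed 5% Fisher test at OR 4.8, but the analysis text never carries that test forward; read two-sided, power is 70% with Fisher and 79% with uncorrected chi-squared

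*Protocol article*

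**What the plan says.** All of this is in the Protocol article, Statistical methods.

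- **Sizing.** The calculation is made "considering a power of 0.80 and a confidence level of 95% (one-tailed" Fisher's exact test). On the effect, "the effect size was set at an OR of >4.8". The fusion rates behind it are given for the arm with "vBMA clot combined with allogeneic bone chips (>91" percent), "compared to the group treated with allogeneic bone chips alone (<70" percent). The result is a minimum of 58 per group, with 20% drop-out included.
- **Threshold.** A p-"value of < 0.05 is considered statistically significant". This applies to all analyses, and sidedness is not mentioned.
- **Test.** For dichotomous data, Fisher's "Exact test or chi-squared test is used to compare proportions between the two treatments", with logistic models for regression. No direction is given, no choice is made between the two tests, and the article does not say whether the chi-squared test is continuity-corrected.
- **Intervals.** For the logistic models of the dichotomous fusion outcome, "The results are reported as odds ratios (ORs) with corresponding 95% confidence intervals (CIs").

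The word one-tailed appears only in the sample size paragraph. The article does not use the word two-sided and gives no reason for a one-tailed design.

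**The concern.** The sample size and the inference appear to rest on different tests. A 95% confidence interval for an odds ratio conventionally goes with a two-sided 5% test. If the primary comparison is judged that way, the 80% power was calculated for an easier hurdle than the one the trial will face.

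If the comparison is instead judged one-tailed at 5%, the stated power stands. A result could then be declared significant while the 95% interval printed beside it includes an odds ratio of 1. Either way something has to be reconciled.

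The open choice between Fisher and chi-squared adds to this. At this sample size the two differ by about 10 points of power and also in true type I error. If the choice were made after seeing the data, it could decide a borderline result.

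**Working it through.** **Inputs (Statistical methods).** Power 0.80; alpha 0.05 one-tailed; Fisher's exact test; OR 4.8, experimental rate 91% and control rate 70%, each taken at the boundary of the stated inequality; 58 per arm including 20% drop-out; two equal arms.

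**Step 1: evaluable patients.** 58 × (1 − 0.20) = 46.4, so 46 per arm. In the other direction, 46 / 0.80 = 57.5, which rounds up to 58.

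**Step 2: experimental rate implied by OR 4.8.** Control odds = 0.70/0.30 = 2.333. Experimental odds = 4.8 × 2.333 = 11.2. Rate = 11.2/12.2 = 91.8%.

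**Step 3: odds ratio implied by 91% versus 70%.** (0.91/0.09) / (0.70/0.30) = 10.111/2.333 = 4.33. The stated rates, taken at their boundaries, are therefore a smaller effect than the stated odds ratio.

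**Step 4: power.** Power is the sum, over all pairs (x, y) that the test rejects, of Bin(x; n, p1) × Bin(y; n, p2), with every 2×2 table enumerated.

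*Reproducing the plan.* One-tailed Fisher at 5% with 91.8% versus 70% gives 79.1% at 45 per arm and 80.2% at 46. The smallest n reaching 80% is 46, which inflates to the stated 58. At 91% versus 70% the same test gives 76.2% at 46 and needs 51 evaluable (51/0.8 = 63.75, so 64 enrolled). The published figure therefore rests on OR 4.8.

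*Changing the test, 46 evaluable per arm:*

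| Test at 5% | OR 4.8 (91.8% vs 70%) | 91% vs 70% (OR 4.33) |
|---|---|---|
| Fisher, one-tailed (as sized) | 80.2% | 76.2% |
| Fisher, two-sided | 69.8% | 64.9% |
| Chi-squared with continuity correction, two-sided | 69.1% | 64.4% |
| Chi-squared, uncorrected, two-sided | 79.4% | 75.2% |
| N-1 chi-squared, two-sided | 79.4% | 75.1% |
| Boschloo, two-sided | 77.2% | 73.0% |
| Unadjusted logistic, Wald, two-sided | 75% | 72% |
| Unadjusted logistic, likelihood ratio, two-sided | 80% | 76% |

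**Step 5: separating the two effects.** Sidedness alone, with Fisher at OR 4.8, costs 80.2 − 69.8 = 10.4 points. Moving from OR 4.8 to 91% versus 70% costs 69.8 − 64.9 = 4.9 points with two-sided Fisher, and already costs 80.2 − 76.2 = 4.0 points in the one-tailed design.

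**Step 6: sensitivity to drop-out.** If all 58 per arm are evaluable, two-sided Fisher gives 81.5% (OR 4.8) or 77.3% (91% versus 70%).

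**Step 7: patients needed for 80% with two-sided Fisher.** OR 4.8 needs 57 evaluable (57/0.8 = 71.25, so 72 enrolled) per arm. For 91% versus 70% it is 62 evaluable (62/0.8 = 77.5, so 78 enrolled).

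**Step 8: true type I error at 46 per arm (maximum over the common fusion rate).** One-tailed Fisher 3.8%; two-sided Fisher 3.0%; N-1 chi-squared 5.3%; uncorrected chi-squared 6.1%. Boschloo stays at or below 5% by construction.

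**The case against.** A reader might infer that the trial's real power is 65–70% and that the 80% claim is simply false. The documents do not support that, for four reasons.

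1. The article states no two-sided rule. The only sidedness it gives is one-tailed. The p<0.05 threshold is general, and the 95% intervals belong to the regression text. If the primary test is the one-tailed Fisher test used for sizing, power at OR 4.8 is 80.2%, as stated.
2. The 65–70% range applies only to two-sided Fisher (continuity-corrected chi-squared is about a point lower at each end). The plan also permits chi-squared, which uncorrected gives 79.4% at OR 4.8, and logistic models, which give 72–80%.
3. The 65% end combines two issues. Part of it comes from the gap between OR 4.8 and 91% versus 70%, which lowers power in the one-tailed design too. The article also writes the rates as above 91% and below 70%, so this is the least favourable boundary.
4. These figures assume that the full 20% is lost. With no loss, two-sided Fisher reaches 81.5% at OR 4.8. The article also says that missing values may be imputed.

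Nor should the one-tailed option be read as doubling the error rate from 2.5% to 5%. Fisher is conservative, and its true one-tailed size here is at most 3.8%.

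These points limit the size of the claim, but the mismatch remains. It is not a detail that can be left to an analysis plan, because the article fixes both the sidedness used for the sample size and the interval and threshold used for the results, and the two do not match. A later analysis plan that adopted a two-sided 5% Fisher test would leave the 80% wrong.

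**Conclusion.** The point holds as a mismatch between the sizing test and the inference text. The 80% is correct for one combination only: one-tailed 5% Fisher, OR 4.8, 70% control fusion and 46 evaluable per arm. Under the two-sided reading that the 95% intervals imply, the shortfall at OR 4.8 is about 10 points with Fisher (70%) or corrected chi-squared (69%), and under one point with uncorrected or N-1 chi-squared (79%). At 91% versus 70% every test in the table falls below 80%, including the one-tailed Fisher test (76%).

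This conclusion assumes that two-sidedness may be inferred from convention, that the full planned drop-out occurs, and that the stated rates and odds ratio are taken at their boundaries. It bears on the power and error rate of the primary comparison and should be settled before unblinding.

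**What to change.** For the primary fusion outcome, replace the open choice of tests with a single named two-sided 5% test that is consistent with the 95% confidence interval. A test less conservative than Fisher is preferable: Boschloo's exact test, which keeps its size at or below 5%, or the N-1 chi-squared test, whose maximum size is about 5.3%. Fisher is also valid, at a lower power.

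Restate the power for the chosen test at 46 evaluable per arm: about 73–77% for Boschloo, 75–79% for N-1 chi-squared, or 65–70% if Fisher is kept. Say which effect each figure refers to, since OR 4.8 and 91% versus 70% are not the same assumption.

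If the one-tailed test is to be kept, state it for the analysis as well as the sizing, justify it, and report intervals that match it (a one-sided 95% bound or a 90% two-sided interval). The 80% at OR 4.8 then stands.

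The cost is wording in the protocol and analysis plan. No extra patients are needed, but under the two-sided option the stated power is less favourable and stays below 80%. Restoring 80% with two-sided Fisher would take 72 to 78 enrolled per arm.

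### The sample-size paragraph pairs an odds ratio of 4.8 with fusion rates of 91% and 70%, which give 4.33; 58 per arm has 80% power at the first and about 76% at the second

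*Protocol article*

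**What the plan says.** All of this is in the protocol article, Statistical methods, first paragraph.

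- Design: "considering a power of 0.80 and a confidence level of 95" per cent, with a "one-tailed Fisher’s exact test".
- Effect size: "the effect size was set at an OR of >4.8, assuming a higher SF percentage in the group treated with vBMA clot".
- Rates attached to it: the clot "combined with allogeneic bone chips (>91%) compared to the group treated with allogeneic bone chips alone (<70" per cent).
- Result: at least 58 patients per group, "including a 20% drop-out rate".
- Evidence offered, first study: 90% fusion with autograft plus demineralized bone matrix, "compared to 70% in those treated with allograft and bone marrow aspirate (BMA) (OR = 3.9").
- Evidence offered, second study: 93% with allograft plus bone morphogenetic protein, "compared to 73% of those treated with allograft alone (OR = 5.3").

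The article moves from these two studies to 4.8 without showing how the value was obtained.

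**The concern.** An odds ratio and a pair of rates are two descriptions of one alternative, so they must agree. Here they do not, and the required sample size differs between them. Someone who takes the rates at face value will believe that the trial has 80% power to detect 91% against 70%. Someone who takes the odds ratio will believe that it has 80% power for a slightly larger effect. This paragraph is the only justification given for the number of patients on the primary outcome, and the effect it names is the one against which a non-significant result will be read.

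The route to the value is also thin. Neither cited comparison is the trial's own contrast of marrow plus allograft against allograft alone. In the first, allograft plus bone marrow aspirate is the arm with the lower rate (70%). In the second, the added agent is bone morphogenetic protein, not marrow. The odds ratio printed for the second study is not the one that its printed percentages give.

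**Working it through.** **Inputs** (Statistical methods): one-sided alpha 0.05, power 0.80, Fisher's exact test, equal groups (one n is given for each group), drop-out 20%, odds ratio 4.8, rates 91% and 70%.

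**Formulas**
- OR = [p1/(1 − p1)] / [p0/(1 − p0)], where p1 is the experimental rate and p0 the control rate.
- Exact power = the sum of the two binomial probabilities over every pair of outcomes for which the one-tailed Fisher p-value is at most 0.05.
- Randomised per arm = evaluable / (1 − 0.20), rounded up.

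**Step 1. Reproduce the plan's figure.** Take p0 = 0.70 and OR = 4.8. The experimental odds are 4.8 × 0.70/0.30 = 11.2, so p1 = 11.2/12.2 = 0.918. The smallest n with power of at least 0.80 is 46 per arm (power 0.8015). Then 46/0.80 = 57.5, so 58. This matches the plan exactly. Holding the odds ratio at 4.8 but fixing the experimental rate at 91% implies a control rate of 67.8%, which needs 44 evaluable and 44/0.80 = 55 randomised. That does not match.

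**Step 2. Odds ratio at the printed rates.** (0.91/0.09)/(0.70/0.30) = 10.11/2.333 = 4.33.

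**Step 3. Power and sample size at each pair of rates** (one-tailed Fisher, alpha 0.05)

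| Rates | OR | Power, 46 evaluable per arm | Evaluable per arm for 80% | Randomised per arm |
|---|---|---|---|---|
| 91.8% vs 70% | 4.80 | 80.2% | 46 | 58 |
| 91% vs 70% | 4.33 | 76.2% | 51 | 64 |
| 90% vs 70% (first cited study) | 3.86 | 71.0% | 56 | 70 |
| 93% vs 73% (second cited study) | 4.91 | 76.8% | 50 | 63 |

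At 91% versus 70%, 50 per arm give 0.799 and 51 give 0.808; 51/0.80 = 63.75, so 64. If nobody drops out, 58 per arm give 86.3% at these rates.

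**Step 4. The cited odds ratios.**
- First study: (0.90/0.10)/(0.70/0.30) = 3.86, which agrees with the printed 3.9.
- Second study: (0.93/0.07)/(0.73/0.27) = 4.91, against the printed 5.3. If both percentages were rounded to whole numbers, the odds ratio could lie anywhere from (0.925/0.075)/(0.735/0.265) = 4.45 to (0.935/0.065)/(0.725/0.275) = 5.46. The value 5.3 is inside that range.

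**The case against.** The strongest defence is that the article defines the effect size as an odds ratio, and that 58 per arm is right for 4.8. This stands. A reader might infer that the trial does not deliver its stated 80% power. The document does not support that without qualification, because 80% is delivered at the odds ratio that was used.

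The second defence is that the rates are inequalities. Some pairs inside them do reach both targets: 91.5% versus 69% has an odds ratio of 4.84 and 81.7% power with 46 per arm. This is true, but the two bounds together guarantee only an odds ratio above 4.33, so 4.8 does not follow from them. Rounding does not close the gap either: the largest odds ratio from rates that round to 91% and 70% is (0.915/0.085)/(0.695/0.305) = 4.72. At that extreme 46 per arm would still give 80.2%, so rounding can save the sample size but not the printed odds ratio.

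Three further inferences are tempting and should not be drawn.

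- **That 5.3 is an error.** It is compatible with rounded percentages, and the source is not at hand. It needs checking, and no more can be said.
- **That 4.8 is a miscalculated average of the cited odds ratios.** The article never calls it an average, and it lies between them, both as printed (3.9 and 5.3) and as recomputed (3.86 and 4.91).
- **That the cited rates show no benefit of marrow,** by setting 70% (allograft plus aspirate) against 73% (allograft alone). Those are single arms of different studies. The Introduction also distinguishes clotted from liquid aspirate, reports fusion in all 10 pilot patients treated with the clot, and gives pseudarthrosis rates of 25–35%. Those imply 65–75% fusion, which is in line with a 70% control rate.

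**Conclusion.** The sample-size statement is internally inconsistent. The printed bounds give an odds ratio of 4.33, not 4.8, and the planned number follows the 4.8. Read at 91% versus 70%, power after drop-out is 76.2%, which is 3.8 points below the stated 80%. Restoring 80% there would take 6 more randomised patients per arm (64 against 58; 128 against 116 in total). That shortfall assumes that the bounds are the intended rates, that the full 20% drop out, and that the one-tailed exact test is used.

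The size is modest and the planned number need not be called wrong. What is wrong as written is that the paragraph names two different alternatives for one sample size. In addition, the cited studies bracket 4.8 but neither derives it nor tests this trial's comparison, so the value is best understood as a target.

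**What to change.** Rewrite the sample-size paragraph as follows.

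1. State one pair of rates with its matching odds ratio and power. Either 91.8% versus 70%, odds ratio 4.8, power 80%; or 91% versus 70%, odds ratio 4.33, power about 76% with 46 evaluable per arm. Give the rates as values, without inequality signs.
2. Say how the value was chosen and call it a target difference. Acknowledge that neither cited study compares marrow plus allograft with allograft alone, and that allograft plus aspirate was the lower arm in one of them.
3. Check the odds ratio of 5.3 against the source. If it comes from unrounded data, say so; if not, print the value that the percentages give (4.91).

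The cost is wording only. No patients are added under either option; under the second, the stated power becomes slightly lower.

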### Objectives and trial design

An RCT has been designed to evaluate the efficacy of autologous vBMA clots in SF procedures for patients with lumbar degenerative spine diseases. The study compares two groups: patients treated with autologous vBMA clots combined with bone allograft chips versus those receiving bone allograft chips alone (standard treatment). Additionally, the study assesses whether patient age and gender influence clinical outcomes.

As secondary objectives, this study aims to characterize platelet-specific parameters, cytokines/chemokines, growth factors, pro-inflammatory and anti-inflammatory markers, and MSCs that define the vBMA clot through molecular and cellular analyses. To further investigate its intrinsic biological potential, an advanced humanized three-dimensional (3D) *in vitro* SF model is developed. All experimental setups will consider age and gender differences, including an evaluation of their interactions.

Furthermore, the study examines the antibacterial properties of vBMA clot against common Gram-positive and Gram-negative bacteria associated with spinal infections, including methicillin-sensitive and methicillin-resistant *Staphylococcus aureus* and *Escherichia coli*. *In vitro* time-kill and bacterial adhesion assays are conducted to assess the ability of vBMA clot to inhibit bacterial growth as well as analyze the potential variations related to patient age and gender.

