### Eligibility criteria

The inclusion criteria are men or women aged between 18 and 80 years at the time of surgery and patients with radiologically diagnosed spinal disorders who are candidates for posterior SF involving ≤5 levels, either posterolateral or interbody fusion, with pedicle screw fixation, excluding cases with standalone posterolateral fusion.

The exclusion criteria include patients with systemic infections (e.g., HIV, HBV, or HCV); those with coagulation disorders; pregnant or breastfeeding women; those with oncological diseases; those with local infectious diseases (e.g., tuberculous spondylodiscitis and suppurative spondylodiscitis); a history of previous spinal surgery; those undergoing radiotherapy or chemotherapy; those with myeloproliferative disease; those receiving steroid therapies; those with untreated thyroid disorders; immunosuppressed patients; those with traumatic spinal conditions; and those with osteoporotic conditions affecting spinal integrity.

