### Scientific relevance and broader impact

The main challenge of SF surgery is to have a safe, functional, high-quality, and easy-to-use therapeutic strategy to improve surgery success and health-related quality of life, as well as in those patients with higher revision rates, such as female and elderly patients. The biological steps involved in creating a bony fusion between adjacent segments of the spine are a complex and highly coordinated series of events. In this context, the relevance of this research is to provide evidence on the potentiality of the vBMA clot as an autologous and multifunctional bioscaffold that can target all the main key challenges for SF surgery. First, the vBMA clot may act as an osteogenic and osteoinductive 3D bioscaffold containing pluripotent mesenchymal and hematopoietic stem cell that work synergistically to foster bone formation and regeneration. Second, platelet degranulation in the vBMA clot allows the release of various biomolecules (alpha granules, platelet-specific proteins, cytokines/chemokines, growth factors, coagulation factors, and adhesion molecules), which may promote early vascularization, a process vital for bone homeostasis, healing, regeneration, and the osseointegration of fixation hardware. Third, mesenchymal progenitors in the vBMA clot may modulate inflammation through a paracrine immunomodulatory effect, enabling an optimal transient stage of acute inflammation, which is a key element for successful bone healing. Fourth, an additional powerful element of the vBMA clot could be the critical role of the coagulation cascade and bone marrow MSCs in the early innate immune system activation and in their involvement in stressing and eliminating bacteria. The ability of the vBMA clot to provide a local combined delivery system of stem cells, signaling biomolecules, and anti-inflammatory and antibacterial factors, all enclosed by a matrix molded by the clot, represents an advanced and simple strategy to meet the main clinical needs of SF. vBMA is harvested simultaneously during the preparation of the site for pedicle screw insertion, and after clotting (~15–20 min), it is reintroduced in association with a bone allograft at the fusion site, without additional surgical time or donor site involvement. This approach offers a single, safe treatment while eliminating the need for *ex-vivo* cell manipulation, synthetic induction factors, or complex fabrication processes, thus providing a ‘One-Health’ strategy for SF surgery with a significant impact on patients.

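### Age is a stated objective and is recorded as continuous, yet the fusion model fixes it as categorised, which costs power for an age effect that the trial can already detect only if it is large

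*Protocol article*

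**What the plan says.** Under Objectives and trial design, the protocol article adds an aim to the treatment comparison: "the study assesses whether patient age and gender influence clinical outcomes". The Outcomes section repeats it for the fusion rate. Eligibility admits "men or women aged between 18 and 80 years at the time of surgery".

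Under Statistical methods, the dataset is described as holding "continuous variables (e.g., age, growth factor expression, and bacterial time kill results" and so on, so age is recorded on its natural scale. The same section says that "the variable of the primary outcome is dichotomous (fusion or no fusion" and that "it is analyzed in relation to age (categorized) and gender through logistic regression models". It gives no reason for grouping age and no fusion analysis with age kept continuous. The grouping is stated for fusion only, not for VAS, ODI or SF-36.

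**The concern.** Grouping a continuous predictor treats everyone within a band as alike and discards the ordering inside it. Where the predictor is the subject of an objective, that is a direct cost to the question asked. The cost matters more here because the outcome to be explained, non-fusion, will be rare, and an age test with little power may return a non-significant result whether or not age matters. At stake is the credibility of what the trial reports about age: a real gradient could be missed, and a null result could be taken as reassurance.

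**Working it through.** **1. The plan's own sample size.** Inputs from Statistical methods: fusion 70% with allograft alone, OR 4.8, one-tailed Fisher's exact test at 5%, power 0.80, 20% drop-out.
- Experimental odds: 4.8 × 0.70/0.30 = 11.2, so the rate is 11.2/12.2 = 0.918.
- Exact power reaches 0.802 at 46 per group, and 46/0.80 = 57.5, rounded up to 58. The stated 58 per group is reproduced.

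**2. Expected non-fusions among completers.**
- With the stated 91%: 46 × 0.30 + 46 × 0.09 = 13.8 + 4.1 = 17.9.
- With 91.8%: 17.6.
- With no drop-out at all (58 per group): 22 to 23.

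**3. Power for an age effect.** The article gives neither an age distribution nor an age effect, so both are assumed. Logistic models were simulated (2,000 trials per scenario) with treatment and gender included and non-fusion of 30% and 9%. There were 48 completers per arm, slightly more than 46, giving about 18.7 non-fusions. Age was tested by a two-sided 5% likelihood-ratio test. The true effect was linear on the logit. Ages were either normal (mean 60, SD 12, truncated to 18–80, resulting SD 10.8) or uniform on 18–80 (SD 17.9).

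| Ages | OR per SD | Continuous | Median split | Cut at 65 | Tertiles (2 df) | Quartiles (3 df) | Tertile score (1 df) |
|---|---|---|---|---|---|---|---|
| Normal | 1.5 | 33% | 24% | 22% | 23% | 23% | 29% |
| Normal | 2.0 | 65% | 48% | 45% | 47% | 47% | 56% |
| Normal | 2.5 | 87% | 71% | 68% | 71% | 70% | 82% |
| Uniform | 1.5 | 34% | 27% | 24% | 24% | 23% | 30% |
| Uniform | 2.0 | 70% | 58% | 50% | 56% | 53% | 66% |
| Uniform | 2.5 | 88% | 78% | 69% | 76% | 75% | 84% |

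With SD 10.8, an OR of 2.0 per SD is 2.0^(10/10.8) = 1.90 per decade.

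- Loss from two groups or unordered bands: smallest 33.6 − 26.6 = 7.0 points, largest 70.4 − 49.8 = 20.6 points.
- As a share of power, normal ages: 9.1/32.7 = 28% to 10.7/32.7 = 33% at OR 1.5, and 17.2/65.2 = 26% to 19.8/65.2 = 30% at OR 2.0. The share is smaller at OR 2.5 (15.2/86.6 = 18% to 18.4/86.6 = 21%) and for some groupings of uniform ages.
- Loss from an ordered tertile score: 3.6 to 8.9 points.

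**4. Cross-check with 92 completers and a slope per year.** Absolute power varied between runs, apparently with how the age limits were imposed, but the gap was stable. At 0.05 per year, continuous age gave 46–54% against 30–38% for two-group cuts. At 0.07 it gave 71–80% against 52–64%. Within runs the gap was 11 to 19 points. A far off-centre cut at 70 lost more (47% to 24%, and 73% to 41%).

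**5. Information kept.** The squared correlation of grouped with continuous age is 0.66 to 0.75 for a median split, 0.55 to 0.56 for a cut at 65, and 0.81 to 0.89 for a tertile score. A two-group split therefore acts like losing 17.9 × 0.25 = 4.5 to 17.9 × 0.45 = 8.1 of the non-fusions.

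**The case against.** The strongest reply is that the loss depends on the assumed shape. A linear truth favours a linear term. With a true step at 65, the order reverses: at a log-odds step of 1.0, a cut at 65 has 45% power against 32% for continuous age, and at 1.4 it has 70% against 51%. This stands, but only when the cut matches the step; a mismatched cut falls to 26% and 42%, below continuous age. The article argues for no threshold.

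It is also fair that the number of bands and the cut-points may sit in the full protocol, so their absence is not a fault here. The point rests only on the stated decision to group. An ordered score would make the loss small, but the article does not say that one is intended.

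Some stronger readings are tempting and are not supported:
- A reader might infer that crossing age group, gender and arm leaves cells with no non-fusions. For an experimental arm split into cells of 12, 12, 11 and 11 at 9%, the chance of at least one empty cell is indeed 1 − (1 − 0.91^12)²(1 − 0.91^11)² = 0.81. But Statistical methods states no such crossing for fusion; interactions of age and gender are mentioned for the laboratory work. In a main-effects model, some factor level lacks non-fusions in only about 1–2% of trials, mostly the experimental arm itself, which continuous age would not cure.
- A reader might infer that the small event count causes the proportional loss. It does not; it makes power low under either coding.
- A reader might link a null age test to the Introduction's claim about donor age. That claim concerns the biological properties of the clot, not fusion rates. The remark on elderly and female patients under Scientific relevance and broader impact is context, not a subgroup hypothesis.

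**Conclusion.** The point holds at moderate weight. The article fixes an information-losing coding of age for a stated objective without giving a reason. If the effect is roughly linear on the logit, common groupings cost about 7 to 20 percentage points of power, which is about a quarter to a third of the power for ORs of 1.5 to 2.0 per SD with ages centred near 60. The figures rest on assumed age distributions, assumed slopes, a two-sided 5% test and about 18 non-fusions.

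It would go too far to say that grouping removes most of the trial's ability to detect an age effect. Keeping age continuous does not rescue the objective either: power is then still only about a third at an OR of 1.5 per SD and 65–70% at 2.0. The treatment comparison and the 58 per group are untouched. The change is advisable rather than essential.

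**What to change.** In the fusion model under Statistical methods, replace the categorised age term with age as a continuous linear term, reported per decade, alongside treatment and gender. Check linearity with at most one low-df term, since about 18 events will not carry more. Show fusion by age band descriptively only. Add a sentence that a non-significant age test will not be read as evidence that age has no effect. Any treatment-by-age or treatment-by-gender term is optional; if used, label it exploratory and fit it by penalised likelihood (for example Firth).

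The cost is an amendment to the analysis text before the data are analysed, with no new data or patients. The downsides are that the result is expressed per decade instead of per age group, and that a sharp threshold effect would be detected less well.
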